**Fig. 1 Fig1:**
[figure not shown]
CONSORT trial flow diagram

To be able to detect a change of two additional help seeking resources [11], with 80% power at the 0.05 alpha level, assuming that the mean in the control group is 1 and in the intervention group 3 with a common standard deviation of 8, 506 participants are required, increasing to 596 allowing for 15% attrition at 6 months. Pilot data indicates a response rate of 40% across organisations and an average cluster size of 72 employees (calculated from organisations currently signed up) therefore approximately 29 employees per organisation (cluster size). With 24 clusters, 12 organisations per condition, and assuming an intraclass correlation coefficient (ICC) equal to 0.01 (ICC’s are lower for participant outcomes as opposed to process variables, when cluster size is large and when estimates are adjusted by participant baseline characteristics [21]), a minimum target sample size is 763, rounded up to 800, 400 per condition

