### Statistical methods

#### Statistical methods for primary and secondary outcomes {20a}

All outcomes will be described with the appropriate descriptive statistics: mean and standard deviation for continuous outcomes (or medians and interquartile range for skewed data) and counts and percentages for dichotomous and categorical outcomes.

The analysis of the primary outcome will estimate the mean difference (with 95% confidence intervals) in the Actual Help-Seeking score at 6-month follow-up between the intervention (MHFA) and standard care groups using a mixed effects repeated measures model (which assumes incomplete outcome data to be missing at random). The model will incorporate demographic and other baseline covariates as fixed effects. The dependent variable will be the count of help sources on the Actual Help-Seeking questionnaire. The independent variable will be ‘time point’. The effect size of the intervention will be estimated as the exponentiated coefficient for the interaction term between time point (baseline versus 6-month follow-up) and intervention status (MHFA versus control group). A random effect of participant will be included in the model to adjust for the repeated measures on participants. ‘Employing organisation’ will be included as a higher level random effect (with participants nested in employers). Statistical significance will be at the 5% level.

Secondary outcomes will be analysed using an appropriate generalised linear model, for example binary logistic regression for dichotomous outcomes and ordinal logistic regression for ordered categorical outcomes. All models will be adjusted for employing organisation and baseline score (where applicable).

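### As worded, the time-by-arm contrast makes no allowance for organisations that differ in how help-seeking changes; the effect is modest, and larger for all respondents than for recipients

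*Protocol article*

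**What the plan says.** In the protocol article, section 20a (statistical methods for primary and secondary outcomes), the dependent variable is the count of help sources. The effect is the exponentiated coefficient of "the interaction term between time point (baseline versus 6-month follow-up) and intervention status (MHFA versus control group"). Two random effects are named. One is for participant. The other is for employing organisation, which "will be included as a higher level random effect (with participants nested in employers"). No organisation-by-time term, robust variance or small-sample correction is named. Time point is listed as the independent variable, and an arm main effect is not mentioned.

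For secondary outcomes the same section says: "All models will be adjusted for employing organisation and baseline score (where applicable").

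The sample size section (14) does provide for clustering, "assuming an intraclass correlation coefficient (ICC) equal to 0.01" and taking "approximately 29 employees per organisation (cluster size").

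The primary outcome section makes the analysis of MHFA recipients the primary one and describes them as a small, non-random subsample. The intention-to-treat comparison of all respondents is a further analysis.

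**The concern.** The interaction compares arms on each employee's change from baseline to 6 months. An effect that is constant over time, whether of an employee or of an organisation, adds the same amount to both measurements and drops out of that change. If both random effects are intercepts, the model treats every employee's change as independent. Organisations may nevertheless differ in how help-seeking moves over 6 months. The protocol lets each organisation choose how many staff to train, recruits over a year, and uses an outcome with a 2-week window. Such differences would make the interval too narrow and push the test above 5%, so the clustering paid for in the sample size would not reach the analysis.

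There is a second, separate issue of precision. A change contrast is less efficient than adjusting for baseline when the within-person correlation is low, and baseline is collected before allocation, so adjusting for it is legitimate.

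**Working it through.** **The plan's own figure.** Inputs from the sample size section: "the mean in the control group is 1 and in the intervention group 3 with a common standard deviation of 8", "with 80% power at the 0.05 alpha level". A two-sided t-test needs 253 per arm, 506 in total. 506/(1 − 0.15) = 595.3, so 596. Design effect 1 + (29 − 1) × 0.01 = 1.28, and 596 × 1.28 = 762.9, so 763. All stated figures reproduce.

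**Cancellation.** In one simulated complete dataset (ICC 0.05, organisation autocorrelation 0.5), linear mixed models gave these standard errors for the interaction:

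| Random effects | Complete data | 15% missing follow-up |
|---|---|---|
| Participant only | 0.5867 | 0.6164 |
| + organisation intercept | 0.5867 | 0.6162 |
| + organisation-by-time | 1.1804 | 1.1974 |

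The organisation intercept contributes essentially nothing. With no arm main effect in the model, the complete-data standard error is still understated: 0.560 with the organisation intercept, 1.000 with organisation-by-time.

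**Type I error, all respondents.** From the plan: SD 8 (variance 64), ICC 0.01, 12 organisations per arm, m = 29. Assumed, because the documents give neither: within-employee correlation ρ, and organisation autocorrelation c (the correlation of an organisation's effect between baseline and 6 months). ICC is taken as 0.01 at both times.

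- Between-organisation variance of change: B = 2 × 0.64 × (1 − c)
- Within-organisation variance of change: W = 2 × 63.36 × (1 − ρ)
- True variance of the contrast: (2/12)(B + W/m)
- Variance reported by the random-intercept model: 2(B + W)/(12m)

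At ρ = 0.5 and c = 0.5, B = 0.64 and W = 63.36. The true variance is (2/12)(0.64 + 2.185) = 0.471, SE 0.686. The model reports 2 × 64/348 = 0.368, SE 0.606. The ratio of variances is 1.28, the plan's own design effect. Type I error is 2Φ(−1.96/1.131) = 8.3%.

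| c | ρ = 0.3 | ρ = 0.5 | Simulation, ρ = 0.5 |
|---|---|---|---|
| 1 | 5.0% | 5.0% | 5.0% |
| 0.8 | 5.9% | 6.3% | 6.2% |
| 0.5 | 7.4% | 8.3% | 8.6% |
| 0 | 9.8% | 11.6% | 11.9% |

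With 25 completers per organisation, the same formula at ρ = 0.3 gives 5.8%, 7.0% and 9.1% for c = 0.8, 0.5 and 0. At ρ = 0.7 and m = 29 it gives 7.2%, 10.5% and 15.7%. A t-test on organisation-level change with 22 df held 4.7% to 5.5% in every simulated scenario, including those with ICC 0.03 and 0.05.

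**Type I error, recipients only.** The number of recipients per organisation is not given; I assume 4. At the unfavourable end (ρ = 0.5, c = 0) the ICC of change is 1.28/(1.28 + 63.36) = 0.0198.

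- With 4 per organisation in both arms, the variance ratio is 1 + 3 × 0.0198 = 1.059 and type I error is 5.7%.
- With 4 per MHFA organisation and 25 per control organisation, the ratio is (1.059/48 + 1.475/300)/(1/48 + 1/300) = 1.117 and type I error is 6.4%.

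Simulations with 3 to 5 recipients per organisation gave about 5% to 6.5% at c between 0.5 and 0.8, and 5.4% to 7.0% at c = 0.

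**Precision, if an arm main effect is fitted.** Relative to a 6-month-only comparison, the change contrast has variance 2(1 − ρ) and the baseline-adjusted one 1 − ρ², a ratio of 2/(1 + ρ). On the 506/SD 8 figures, power = Φ(2.80/√v − 1.96), where 2.80 = 1.96 + 0.84.

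- ρ = 0.3: v = 1.40 gives 66%; v = 0.91 gives 84%; ratio 1.54.
- ρ = 0.5: v = 1.00 gives 80%; v = 0.75 gives 90%; ratio 1.33.

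**The case against.** The strongest reply is that the damage is conditional and falls mainly on an analysis that is not the primary one. If organisation effects are fully stable the interval is correct, and at autocorrelation 0.8 with the planned ICC the excess is about one percentage point. The primary analysis is restricted to recipients, and with a few per organisation there is little clustering to miss. Both points stand. A reader might infer that the primary test runs at 7-10%, or at 13-15% with very unequal organisations. The documents do not support that. Those figures are for all respondents, and the highest need uncorrelated organisation effects and a coefficient of variation of organisation size of about 1, neither of which is stated.

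The article never uses the word intercept, and a fuller plan could add an organisation-by-time term. That is fair, but the section does set out a specific model with two random effects and a specific contrast, and followed as written it has this property.

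The efficiency loss is not certain either. No arm main effect is named, and without one the model is in effect a common-baseline model, for which the loss largely goes away. The understated standard error remains.

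The exponentiated coefficient implies a log link, whereas the demonstration is linear. For a Poisson log-link model, cancellation follows by conditioning on each employee's total; that was reasoned, not simulated.

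Finally, a reader might take adjustment for employing organisation in the secondary models to mean fixed effects, which would be collinear with arm. The text does not say fixed, and the preceding paragraph makes organisation random. This needs clarifying and is not a demonstrated error.

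**Conclusion.** The point holds in a limited form. With random intercepts only, the planned interaction gives essentially no protection against organisations differing in change over time, while the sample size assumes that clustering matters. At ICC 0.01, 25 to 29 employees per organisation and within-person correlation 0.3 to 0.5, the nominal 5% test of all respondents runs at about 5% with stable organisation effects, rising to 9-12% when they are uncorrelated over time. The recipient analysis stays at about 5-7%. It would go too far to say that the plan ignores clustering outright or that its primary test is invalid, because both depend on an autocorrelation the documents do not give. The loss of precision is real only if an arm main effect is fitted, and matters mainly when the within-person correlation is below 0.5. It costs power without biasing the result.

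**What to change.** In section 20a:

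- Estimate the 6-month arm difference with baseline AHSQ as a covariate, or state explicitly a longitudinal model with a common baseline mean.
- Add an organisation-by-time random effect, or base inference on organisation-level summaries.
- Use small-sample degrees of freedom for 24 organisations.
- Apply this to both the all-respondent comparison and the recipient analysis.
- As a clarification, say that organisation enters the secondary models as a random effect.

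The cost is wording only, with no new data. The interval will be wider where organisation effects shift over time. At ρ = 0.5 and ICC 0.01, for example, the SE of the change contrast goes from 0.605 to 0.638 at autocorrelation 0.8, and from 0.606 to 0.686 at 0.5. Baseline adjustment recovers some or all of that.

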### Interim analyses {21b}

There will be no interim analyses.

### Methods for additional analyses (e.g. subgroup analyses) {20b}

Age, gender, level of education, ethnicity, nature and frequency of MHFA interventions directly experienced will be included in the primary analysis as covariates.

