### Eligibility criteria {10}

Inclusion criteria are as follows: organisations expressing an interest (directly to MHFAE) in undertaking MHFA training, who have not undertaken this training previously and who agree to participate and are able to provide data on sickness absenteeism, presenteeism and other productivity data. For the purposes of this study, participants will be all employees working in each organisation who provide help-seeking outcome data.

Exclusion criteria are as follows: organisations who have already introduced MHFA across all sites and departments; those who decline to participate in adopting MHFA training; and organisations, employees, mental health first-aiders and recipients who participated in the pilot study.

The intervention will be delivered by qualified MHFAE trainers.

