#### Intervention description {11a}

The MHFA intervention has three parts:
The 2-day MHFA training provided by MHFAE. This is a manualised training programme designed to provide individuals with the following: an in-depth understanding of mental health and the factors that can affect wellbeing, practical skills to spot the triggers and signs of mental health issues, confidence to step in, reassure and support a person in distress, enhanced interpersonal skills such as non-judgemental listening, knowledge to help someone recover their health by guiding them to further support—whether that is self-help resources, through their employer, the NHS, or a combination.Raising awareness of the presence of MHFA in the organisation.The application of MHFA to participants in the workplace. The MHFA training uses a manualised five-stage approach, ALGEE: Approach the person, assess and assist with any crisis; Listen and communicate non-judgementally; Give support and information; Encourage the person to get appropriate professional help and Encourage them to seek other forms of support.

MHFAE recommend training one employee in MHFA per ten employees; however, organisations are free to ask for any number of employees to be trained. The current study will record the ratio of participants trained in each organisation. No stipulation is made as to the selection of participants to be trained, and organisations are encouraged to advertise the training to all staff. The selection criteria used by each organisation will be assessed in the qualitative component of this study.

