### Outcomes {12}

#### Primary outcome

The primary outcome is Employees’ help-seeking behaviour at 6 months measured by the Actual Help-Seeking Questionnaire [AHSQ] [11]. The AHSQ measures help-seeking behaviour in the 2 weeks preceding the assessment and will be assessed at baseline, 6, 12 and 24 months. Help-seeking behaviour is determined by listing the number of help sources, the type of help sought and whether help seeking has occurred during the allocated time period.

The primary analysis will be conducted on those participants who receive MHFA and therefore is a per protocol analysis. Further analyses will examine the impact of the intervention at the organisational level using an intention-to-treat analysis with all respondents included.

As this is a small non-random subsample of randomised participants, it is recognised that this analysis will be vulnerable to selection bias and uncontrolled confounding. For this reason, a range of baseline participant characteristics will be included in the primary analysis to mitigate these limitations.

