#### Secondary outcomes

All secondary outcomes and their measures are described in Table 1. In addition to these outcome measures, the researchers will also capture data on organisations’ sickness absence levels, presenteeism rates and measures of productivity.

**Table 1 Tab1:** Data collection schedule and secondary outcome measures

Measure	Timing of measures				
	Baseline	Post-intervention (up to 3 months)	6 months	12 months	24 months
Demographics (age, gender, level of education, ethnicity, nature and frequency of and MHFA interventions directly experienced, etc.)	X				
Employees help-seeking intentions (General Help-Seeking Questionnaire) [12]	X	X	X	X	X
Employees’ mental health and wellbeing (Warwick-Edinburgh Mental health and Well-being Scale) [13]	X	X	X	X	X
Mental health first aiders’ mental health literacy (Mental Health Literacy Scale) [14]^a^	X	X	X	X	X
Mental health first aiders’ skills (ALGEE scoring system) [15]^a^	X	X	X	X	X
Employees’ quality of life (EQ-5D-5L and Short Form-12 Health Survey SF-12) [16]	X	X	X	X	X
Employees’ self-efficacy (Self-Efficacy for Seeking Mental Health Care Scale) [17, 18]	X	X	X	X	X
Employees’ social well-being (Social Well-being Scale) [19]	X	X	X	X	X
Employees’ use of standard mental health and other services (adapted version of the Client Services receipt Inventory) [20]	X	X	X	X	X

^a^Intervention group

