### Assignment of interventions: blinding

#### Who will be blinded {17a}

Participants, mental health first aiders and researchers will not be blinded to treatment allocation due to the nature of the study. However, independent staff helping to process the data, the trial statistician and health economist will all be blinded to intervention status.

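### The primary model adjusts for MHFA received, which is part of the treatment: near-empty if taken at baseline, and harmful to a degree set by unstated coding if taken later

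*Protocol article*

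**What the plan says.** The protocol article touches this variable in several places.

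- **Additional analyses {20b}.** After age, gender, education and ethnicity, the list ends with the exposure item: "nature and frequency of MHFA interventions directly experienced will be included in the primary analysis as covariates".
- **Secondary outcomes, Table 1.** The demographics row includes "nature and frequency of and MHFA interventions directly experienced" and is marked at baseline only.
- **Intervention description {11a}.** The intervention has three parts, and the third is "The application of MHFA to participants in the workplace".
- **Primary outcome.** "The primary analysis will be conducted on those participants who receive MHFA and therefore is a per protocol analysis". The section concedes that recipients are a selected group and answers that "a range of baseline participant characteristics will be included in the primary analysis to mitigate these limitations".
- **Statistical methods {20a}.** "The model will incorporate demographic and other baseline covariates as fixed effects". The intervention effect is read from the time-by-arm interaction, exponentiated. The same section also names the mean difference at 6 months as the quantity to be estimated.
- **Timing.** Eligible organisations are those "who have not undertaken this training previously" (Eligibility {10}). They are allocated only once baseline measures are complete (Randomisation), and control organisations must hold off MHFA training until the study ends ({11d}).

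**The concern.** A covariate meant to offset selection and confounding has to describe people before treatment. This one describes the treatment. The variable that decides who belongs to the primary population also sits on the right-hand side of the primary model.

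The article does not say when the covariate is measured. Table 1 and the two statements about baseline covariates point to a value taken before allocation, when there is almost nothing to record. The wording of {20b}, which speaks of contacts directly experienced and how often, points to a value taken after MHFA has been delivered. That value is produced by allocation, and it is essentially zero in one arm.

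At stake is the primary estimate. Under some codings it would no longer measure the effect of MHFA, and the result would hang on a choice that the article leaves open. Under none of them does the covariate do the job for which the primary outcome section introduces adjustment.

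**Working it through.** **1. The plan's own figure, to fix the inputs.** From the sample size section: difference 3 − 1 = 2, SD 8, alpha 0.05 (two-sided assumed), power 80%.

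- Normal formula: 2 × 8² × (1.960 + 0.842)² / 2² = 251.2, so 252 per arm and 504 in total. The t-test version needs 252.13, so 253 per arm and 506 in total, as stated.
- Attrition: 506 / 0.85 = 595.3, so 596.
- Design effect: 1 + (29 − 1) × 0.01 = 1.28, and 596 × 1.28 = 762.9, so 763.

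These figures reproduce, and the present point does not change them.

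**2. Covariate taken at baseline.** Write the fixed-effect columns as intercept, arm, time, arm × time and exposure. If nobody has experienced MHFA, the exposure column is all zeros and the matrix has rank 4 of 5: the covariate carries no information. A few employees may have met MHFA elsewhere, so near-constant is the accurate description.

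**3. Covariate taken after allocation.** The model is

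E(Y) = b0 + b1·arm + b2·time + b3·arm·time + b4·X,

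where X is exposure and b3 is the planned effect.

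*Inputs from the article:* 24 organisations of 29 (696 people, 348 per arm), SD 8, ICC 0.01, true effect 2.

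*Assumed:* recipients are compared with control respondents; within-person correlation 0.5; contacts per recipient 1 + Poisson(1), mean 2; in the dose-response case, 1 extra source per contact. As simplifications, all 348 people in the intervention arm are recipients and the fitted model has a random participant effect only. There were 60 simulated trials for the interaction and 40 for row (c).

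*Without X:* SD of change = 8 × √(2 × (1 − 0.5)) = 8, so SE = 8 × √(2/348) = 0.61. The simulation gives 2.04 (SE 0.61).

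| Coding of X | Quantity | Without X | With X |
|---|---|---|---|
| (a) Time-varying frequency, dose-response | interaction | 2.04 (SE 0.61) | 0.09 (SE 0.96) |
| (b) Time-varying yes/no, recipients | interaction | estimable | not estimable, rank 4 of 5 |
| (c) One value per person, main effect | interaction | 2.05 | 2.05 |
| (c) One value per person, main effect | 6-month difference | 1.95 | 0.91 |
| (d) Time-varying frequency, threshold effect | interaction | 1.97 (SE 0.60) | 1.99 (SE 0.95) |

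Why each row comes out as it does:

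- **(a)** b4 absorbs 1 source per contact. b3 becomes the effect of allocation at zero contacts, where there are no recipients; its expectation is 2 − 1 × 2 = 0. In a log-link Poisson version, closer to the planned exponentiated coefficient, the rate ratio goes from 3.61 to 1.02.
- **(b)** Among recipients X equals arm × time, so only b3 + b4 can be estimated. This is exact and needs no assumed figure.
- **(c)** A value that is constant within a person drops out of the change from baseline, so b3 is untouched. b4 is learned from each person's average over the two times, where the slope is (0 + 1)/2 = 0.5. The arm term shifts by −0.5 × 2 = −1, and the 6-month difference b1 + b3 should fall from 2 to 1. The simulated 0.91 has a Monte Carlo error of 0.16.
- **(d)** If any contact gives the full benefit, b4 is zero and b3 stays right, but the variance grows by (0.95/0.60)² = 2.5.

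**The case against.** The best defence is that the planned effect may survive. Section {20a} reads the effect from the interaction and enters covariates as fixed effects. With one exposure value per person as a main effect, the interaction does not move. That stands. The same section, however, also promises a 6-month mean difference, and that quantity is roughly halved.

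Second, on the schedule as printed the covariate is measured before allocation and cannot bias anything. That stands too, and it leaves an adjustment with almost no content. Third, the large loss in row (a) needs a time-varying coding and a dose-response, and row (b) needs a yes/no item. The article states none of these, so neither can be presented as what will happen.

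A reader might infer more than the documents support:

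- *That the covariate must either remove the effect or be empty.* Rows (c) and (d) show intermediate outcomes. Empty is also too strong: eligibility restricts organisations rather than what an employee met elsewhere, and the exclusion covers only organisations that have introduced MHFA throughout.
- *That recipients cannot be identified because Table 1 has no follow-up mark.* Table 1 also omits the AHSQ, which the text schedules at baseline, 6, 12 and 24 months. It is not a complete schedule.
- *That the covariate breaks the statement that "the trial statistician and health economist will all be blinded to intervention status".* A population defined by receipt of MHFA already reveals the arm, so deleting the covariate would not restore blinding.
- *That the all-respondents analysis is affected as well.* Section {20b} assigns the covariate to the primary analysis only.

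**Conclusion.** The point holds in a conditional form. The article commits its primary analysis to adjusting for a component of the treatment, against its own description of the covariates as baseline characteristics. At baseline the item is near-constant and can do little about the confounding that the primary outcome section describes. After allocation, the consequence runs from a 2.5-fold loss of precision, through a 6-month difference cut from 1.95 to 0.91, to an interaction cut from 2.04 to 0.09 or not estimable.

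Which of these applies turns on timing and coding that are not stated. The sizes rest on the assumed correlation, contact distribution and form of effect; the rank results do not. No reading makes the item a useful adjustment for confounding.

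**What to change.** In {20b}, delete the exposure item from the primary covariates and restrict the list to characteristics measured before allocation, in line with the primary outcome section and {20a}. If MHFA met before the study is of interest, a separate baseline item labelled as such does no harm.

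In Table 1, take exposure out of the demographics row and mark it at the follow-up surveys in both arms. It then serves to identify recipients and to check contamination in control. Any dose analysis should be separate and labelled exploratory.

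The cost is one or two items in surveys already being sent, slight respondent burden, and an amendment needing ethics approval under {25}. The sample size is unaffected.
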